## Abstract

**BACKGROUND::**

Interventions capable of modulating the heat shock response (HSR), such as physical exercise and heat therapy (HT), are potential therapeutic strategies for the prevention and treatment of diabetes.

**OBJECTIVE::**

This study aims to evaluate the effects of resistance training (RT) and HT on HbA1c levels, metabolic and inflammatory profiles, gut microbiota, and HSR in patients with type 2 diabetes mellitus (T2DM).

**DESIGN AND SETTING::**

A randomized, double-blind, parallel clinical trial will be conducted for 12 weeks in southern Brazil.

**METHODS::**

Participants with T2DM will be randomized into control (any intervention), RT, or HT groups. In the RT group, participants will perform supervised exercise, and the HT group will undergo whole-body heat treatment in an environmental chamber initially set at 55.0°C, both on three non-consecutive days of the week (60 min). Blood samples will be collected before and after 12 weeks of treatment. Heat shock response, body composition and physical fitness, glycemic control, lipid profile, gut microbiota composition and diversity, inflammatory markers, and flow-mediated dilation will be evaluated.

**CONCLUSION::**

Since the HSR response is decreased in individuals with diabetes, we believe that improving the HSR may be important in preventing chronic complications associated with T2DM. This randomized clinical trial will determine the efficacy of HT compared to RT in improving HSR when combined with conventional therapy in individuals with T2DM. Multiple HT and RT effects may contribute to a lower mortality risk in these individuals.

**CLINICAL TRIAL REGISTRATION::**

Unique Identifier NCT05847075. https://clinicaltrials.gov/study/NCT05847075.

## INTRODUCTION

An estimated 10.5% of all adults aged 20–79 years worldwide have diabetes, and approximately one-third of all deaths in people under the age of 60is attributed todiabetes.^
1
^ The cost of care for diabetes and the associated diseases is very high, but maintaining an individual with diabetes at low or even moderate risk of macro-and microvascular disease is a fraction of what is currently being spent on acute complications.^
2
^For this reason, the search for different strategies to prevent the onset of complications is essential.

One of the main characteristics found in type 2 diabetes mellitus (T2DM), as well as in obese and insulin-resistant individuals, is the chronic presence of low-grade inflammation, which may be related to the expansion of adipose tissue and also to the modification of the gut microbiota profile (gut dysbiosis).^
3
^ Lipopolysaccharide (LPS) produced by gram-negative bacteria cells may induce metabolic endotoxemia and stimulate systemic inflammation, which play a key role in insulin resistance.^
4
^ One of the important responses involved in the resolution of inflammation is the heat shock response (HSR), mediated by the action of 72 kDa heat shock protein (HSP72), whose expression is induced by a wide range of cellular stressors, such as heat, metabolic deprivation, redox imbalance and physical exercise.^
5
^

Dietary, surgical, and pharmacological interventions can alter the gut microbiota of patients with diabetes, leading to an increase in the gram-positive population compared to the gram-negative bacterial population.^
6
^ However, few studies have evaluated the effects of physical exercise on microbiota,^
7-10
^ and the precise contributions of physical exercise, including those related to metabolic endotoxemia in diabetes, remain to be investigated, especially in resistance training. In the context of inflammation, HSP72 is produced in the intracellular environment in response to stressful situations, and has an anti-inflammatory effect, blocking the activation of the main nuclear transcription factor related to inflammation, the nuclear factorkappaB (NF-κB).^
11,12
^ However, in conditions of chronic inflammation and insulin resistance, such as diabetes, the ability of cells to activate the HSR is compromised, causing cellular dysfunction, perpetuation of inflammation, and increased risk of complications in diabetes.^
13
^

Our group recently demonstrated that HSR is blocked in states of insulin resistance (IR), such as diabetes and aging, but can be partially restored by resistance training.^
14
^ Although physical exercise is a very efficient non-pharmacological tool for improving metabolic functions,^
15
^some people have difficulties in performing physical exercise.^
16
^ Therefore, an alternative therapy for special populations, which can induce an increase in HSP70 and other effects similar to those of exercise, is heat therapy (HT).^
17
^ In this sense, interventions capable of modulating the content of HSP72, such as physical exercise and HT, are candidates for the prevention and treatment of insulin resistance and diabetes.

Significantly, new evidence indicates that HT improves glycemic control in healthy individuals and individuals with T2DM by reducing fasting plasma insulin and increasing insulin sensitivity.^
18
^ A recent systematic review and meta-analysis found that HT can benefit people with metabolic diseases.^
19
^ However, only a few studies were included. Further randomized controlled trials with longer intervention and follow-up periods are needed to confirm the beneficial effects of passive heat therapy, which justifies the importance of our protocol in testing the potential benefits of HT for this population.

## OBJECTIVE

Due to few well-conducted clinical trials, we will perform a randomized, three arm, double-blind, parallel study, aiming to compare the properties of resistance training (RT) and HT in type 2 diabetes mellitus (T2DM). We hypothesize that RT and HT will reduce HbA1c levels, improve metabolic and inflammatory profiles, and attenuate gut dysbiosis and the HSR.

## METHODS

### Study design and setting

This prospective, randomized, double-blind, parallel, non-inferiority clinical trial will be conducted at the Universidade Federal do Rio Grande do Sul, a university in southern Brazil. The study protocol adheres to the SPIRIT recommendations.^
20
^

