### Allocation

Participants will be randomly assigned to groups according to a sequence of computer-generated random numbers. This sequence will be obtained in Microsoft Excel (Redmond, Washington, United States) in a 1:1 ratio, with blocks of eight or six participants to complete the total number calculated. A sealed envelope containing the allocation code will be opened at the beginning of the treatment in the presence of the participant according to the order of entry into the study.

Owing to the nature of the interventions, the researcher conducting the exercise sessions and participants will not be blinded. To ensure assessor masking, the participants will be asked to omit their assigned groups and not talk about their interventions during the outcome evaluation sessions. In case of unintentional unblinding for any reason, the researcher will notify the principal researcher.

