### Interventions

Volunteers who met the inclusion criteria will be guided through the study and asked to sign a written informed consent form before enrollment in the trial. The participants will be randomized into the following intervention groups: control, RT or HT. In the control group, participants will not receive any intervention. In the intervention group RT, participants will perform supervised exercises in a gymnasium on three non-consecutive days of the week for a total of 12 weeks. Each session will last approximately 60 min and consist of warm-up, resistance training, and cool-down. All sessions will be conducted by qualified sports and exercise scientists.

The RT program will consist of a combination of upper- and lower-body exercises using gymnasium equipment, free weights, and body weight (functional exercises) as the primary resistance. The 12 weeks RT will be divided into three mesocycles of four weeks each (please see details of sets, repetitions, and intervals in Table 1). The exercises will include leg press, knee extension, leg curl, biceps curl, triceps extension, lat pulldown, shoulder press, bench press, and abdominal crunch exercises. Before the start of the training period, the participants completed a familiarization session to practice the exercises they would perform further during the training program when the exercise load was individually tested. Resistance training was performed using two–three sets per exercise at intensities between 12 and 15 maximum repetitions (the heaviest possible weight to perform 12–15 repetitions), as shown in Table 1. The intensity of the functional exercises was controlled using the OMNI scale,^
21
^ with each session lasting 60 min.

**Table 1 T1:** Resistance training program

Mesocycle	Weeks	Repetitions/load	Number of sets	Interval between sets
**1**	1–4	12/15	2	1 min
**2**	5–8	12/15	3	1 min
**3**	9–12	10/12	3	1 min and 30 s

Participants in the HT group will undertake whole body heat treatment according to previous methods.^
22

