### Statistical considerations

To assess the effect of exercise on plasma HSP levels between the groups post-intervention, we assumed 80% power, 5% significance level, and an effect size (Cohen’s F) of 0.4. We estimated a dropout rate of 10%, and the calculated total number of patients was 22 in each group.^
24
^

The randomly assigned participants’ data will be analyzed according to the intention-to-treat principle as the primary choice and the per-protocol principle, with treatment, time, and treatment-time interaction registered as fixed effects. We will qualitatively document the reasons for, and details of, each withdrawal case. The normality of the data will be tested using the Shapiro-Wilk test. Mean and standard deviation will be used to describe parametric continuous variables, with median and interquartile range for non-parametric variables, and absolute and relative frequencies for categorical variables. Analysis of variance (ANOVA) will be used to compare the final outcomes. Treatment effects (group, time, and group interaction) will be estimated using Generalized Estimation Equations (GEE), followed by the Bonferroni post-hoc test (P < 0.05). Multiple linear regression analysis (backward method) will be performed to investigate the impact of routine pharmacotherapy, sex, and age on the primary and secondary outcomes. SPSS Professional software (version 20.0; IBM Corp., Armonk, New York, United States) will be used for all analyses.

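### The trial is labelled non-inferiority, but it is sized and analysed with tests of difference and has no margin, so it cannot support a non-inferiority conclusion for HT against RT

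*Protocol article*

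**What the plan says.** - **Design label** (Study design and setting): "This prospective, randomized, double-blind, parallel, non-inferiority clinical trial will be conducted". Non-inferiority is mentioned nowhere else in the article.
- **Hypothesis** (Objective): "We hypothesize that RT and HT will reduce HbA1c levels, improve metabolic and inflammatory profiles". This is an efficacy hypothesis for each active arm. The sentence before it gives the aim as a comparison of RT and HT.
- **Comparison of interest** (Abstract, Conclusion; repeated almost word for word in the Discussion): "This randomized clinical trial will determine the efficacy of HT compared to RT in improving HSR".
- **Arms** (Interventions): "The participants will be randomized into the following intervention groups: control, RT or HT".
- **Sample size** (Statistical considerations): Cohen's f of 0.4, 80% power, 5% significance and 10% dropout, giving 22 per group.
- **Analysis** (Statistical considerations): "Analysis of variance (ANOVA) will be used to compare the final outcomes". Treatment effects come from GEE with Bonferroni post-hoc tests at P < 0.05, by intention to treat first and also per protocol.
- **Blinding**: the Abstract (Design and setting), the Objective and the Study design section all say double-blind. The Allocation section says "the researcher conducting the exercise sessions and participants will not be blinded". The Study outcomes section blinds outcome assessors and data analysts.

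**The concern.** A non-inferiority trial needs a reference arm, a margin and a rule that compares a confidence limit with that margin, and its sample size follows from the margin. The article has the label and a pair of arms it wants to compare, but no margin and no rule. What it does fix (the effect size, the ANOVA, the GEE and the post-hoc tests) answers a different question: whether the arms differ. Failing to reject equality between HT and RT does not show that HT is acceptably close to RT, least of all with about 20 people per arm.

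At stake is what the trial may claim about HT against RT. The Introduction presents HT as an alternative for people who have difficulty exercising, and a non-inferiority claim would serve exactly that argument.

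The blinding label is a separate contradiction in the same sentence and has no bearing on the margin.

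**Working it through.** **1. What the stated size is for.** Inputs from Statistical considerations: f = 0.4, alpha 0.05, power 80%. With three equal groups and a one-way omnibus F test, the noncentrality is λ = f² × N.
- n = 21 per group: N = 63, λ = 0.16 × 63 = 10.08, power 0.798.
- n = 22 per group: N = 66, λ = 0.16 × 66 = 10.56, power 0.818.

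So 22 is the smallest group size that reaches 80% for a test of any difference among three arms, before dropout. (Inflating by 10% gives 22/0.9 = 24.4, or 25; that is a separate matter.) No margin enters the calculation.

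**2. Evaluable numbers.** 22 per arm if nobody drops out; 22 × 0.9 = 19.8, about 20, with the planned 10% dropout.

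**3. The margin this size could support for HT against RT.** The article gives neither an SD nor a margin, so the scale is SD units. Assumptions: true difference zero, one-sided 2.5%, post-treatment values with no gain from baseline. By the normal approximation, margin = (1.960 + 0.842) × √(2/n).
- n = 22: 2.802 × 0.3015 = 0.84 SD; by noncentral t, 0.865 SD.
- n = 20: 2.802 × 0.3162 = 0.89 SD; by noncentral t, 0.909 SD.

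**4. Benchmark: the effect implied by f = 0.4.** If RT and HT have equal means and both differ from control by d, the SD of the three means is d × √(2/9). Hence d = 0.4/√(2/9) = 0.4/0.4714 = 0.85 SD. The margin in step 3 is about as large as this whole effect, so an HT no better than control could lie within it.

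**5. Smaller margins and precision.** With half that effect as margin (0.42 SD), noncentral-t power is about 27% at 22 per arm and 25% at 20. The 95% CI half-width for HT minus RT is t × √(2/n): 2.018 × 0.3015 = 0.61 SD at 22, and 2.024 × 0.3162 = 0.64 SD at 20.

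**6. Sensitivity to baseline data.** The GEE includes time, so baseline may help. With baseline correlation r (not in the article, so assumed), the margin is multiplied by √(2(1−r)) for change scores or √(1−r²) with baseline adjustment. At 22 per arm:

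| r | Change score | Baseline-adjusted |
|---|---|---|
| 0.5 | 0.865 × 1.000 = 0.86 SD | 0.865 × 0.866 = 0.75 SD |
| 0.7 | 0.865 × 0.775 = 0.67 SD | 0.865 × 0.714 = 0.62 SD |

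**7. Power if each active arm is instead tested against control.** For d = 0.85 SD, two-sided 5%, power is about 79% at 22 per arm and 74% at 20. With Bonferroni for two contrasts (two-sided 2.5% each) it is about 69% and 64%.

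**The case against.** **Non-inferiority may be the real aim, not a stray word.** The Objective sets out to compare RT and HT, the Abstract and Discussion name HT against RT, the Introduction offers HT as an alternative to exercise, and a per-protocol analysis is planned beside intention to treat. This stands in part: the pair is named, and it would be wrong to say that no comparison is identified. What is absent is a margin and a decision rule for that pair, and the stated sample size was computed for another question.

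**An analysis plan could supply the margin.** It could, but the article already fixes a difference-based size and difference tests. A margin added later would not make that size fit.

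**The margin figures are conditional.** This stands. A reader might infer that 0.86 to 0.91 SD is the only margin the trial could support. That ignores any gain from baseline, and the 0.85 SD benchmark holds only if RT and HT are equal.

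**Misuse is not announced.** A reader might infer that the sponsor plans to treat a non-significant HT against RT result as non-inferiority. No section says so. The label leaves that reading open and nothing rules it out.

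**Blinding is openly described.** This also stands: the Allocation and Study outcomes sections say who is and is not blinded, so the fault is in the label. A reader might infer that the primary outcome is compromised. The article does not support that: it is the heat shock response, measured by immunoassay of HSP72 in blood after incubation. Effort-dependent measures such as peak oxygen uptake are secondary.

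**Conclusion.** The contradiction is real. The Study design section claims a design property that the Statistical considerations section does not deliver, and as designed the trial cannot support a conclusion that HT is non-inferior to RT. Calling the existing design a superiority trial would also be loose: the size is for an omnibus test and powers no particular pair.

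The size of the problem, at a true difference of zero, one-sided 2.5% and no gain from baseline: a margin of about 0.86 SD (22 per arm) or 0.91 SD (20 per arm) for 80% power, against an implied active-versus-control effect of 0.85 SD if RT and HT are equal. A strong baseline correlation would bring the margin down, to about 0.62 SD at an assumed correlation of 0.7 with baseline adjustment and 22 per arm. That would still be nearly three quarters of the benchmark effect (0.62/0.85 = 0.73).

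The double-blind label is a separate, smaller error of description.

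**What to change.** 1. In Study design and setting, delete the non-inferiority label and describe the trial as a test of differences among the three arms, as it is sized.
2. In Statistical considerations, add that HT minus RT will be reported with a 95% CI, and that a non-significant difference will not be taken as non-inferiority or equivalence.
3. If RT against control and HT against control are to be named as the main contrasts, state their power: for 0.85 SD, about 69% at 22 per arm and 64% at 20 with Bonferroni for two contrasts. This would also move HT against RT, the comparison the article names, into second place, so it is a decision for the sponsor and not only wording.
4. Separately, in the Abstract, the Objective and Study design and setting, replace the double-blind label with outcome-assessor- and analyst-blinded, to agree with Allocation and Study outcomes.

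Items 1, 2 and 4 are wording and need no more participants. The cost is giving up a non-inferiority claim. If the sponsor wishes to keep that claim, the alternative is a justified margin for HT against RT, a confidence-interval rule and a new sample size.

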### Eligibility criteria

Participants will be included if they have type 2 diabetes (previously diagnosed by their personal physicians), were between 18-65 years old, with HbA1c levels between 7.0% and 10%, are sedentary non-smokers, body mass index (BMI) between 18.5-39.9 kg/m^
2
^, with controlled blood pressure, and no use of insulin. Participants will be excluded if they are pregnant or breastfeeding; report treatment with antibiotics or anti-inflammatory drugs within four weeks; report a history of myocardial infarction, cardiac illness, vascular disease, stroke, or any condition that would prevent them from engaging in an exercise study; or if they had already been engaged in two or more planned and structured exercise sessions per week (in the last six months).

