^ Participants will be housed in an environmental chamber initially set at 55.0°C on three non-consecutive days of the week. Each session will last 60 min. During the sessions, the rectal temperature, heart rate (HR), blood pressure, and heat discomfort will be constantly measured. According to pilot testing, this protocol induces an approximate 1.2°C raise in the individual’s core temperature and remains increased after the session for an additional 15 min, before it starts to drop (Figure 1a). The HR increases and blood pressure, particularly diastolic pressure, decreases during the session (Figure 1b and Figure 1c, respectively). The core temperature initially decreases (10-15 minutes after the beginning), probably owing to rapid skin vasodilation and a blood flow shift from the center to the periphery. After approximately 20 min in the chamber, the core temperature starts to rise, as expected. The characteristics of the participants from the preliminary study are shown in Table 2.

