### Safety and adverse events

Participants will be under continuous health professional control for at least 30 min after the intervention to prevent adverse events. The following mild and moderate adverse events can occur. Exercise protocols, particularly during maximum effort, can cause discomfort (nausea and muscle soreness). Heat therapy has been shown to be safe for most people.^
17
^ However, for some participants, it is possible that the higher temperature caused thermal discomfort. Cardiovascular changes, such as increased heart rate and blood pressure, are expected and are not harmful. Mild dehydration may be observed after completion of the protocol and will be attenuated by proper hydration.

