## DISCUSSION

Inflammation markers are increased in individuals with diabetes.^
39
^ Strength training has been shown to be a highly efficient therapeutic practice in the prevention and treatment of diabetes,^
15,40
^as it is capable of manage systemic inflammation by decreasing CRP levels, with inconclusive evidence for other inflammatory biomarkers.^
41
^ Furthermore RT leads to subcutaneous abdominal adipose tissue reduction^
42
^ and improves HSR,^
14
^ which could improve T2DM control and prevent chronic complications.

The first study evaluating the effects of HT in diabetes was published by Hooper et al. in 1999, and its primarily resulted in glycemia, HbA1c and body weight decreases.^
43
^ Remarkably, there are few studies analyzing HT and its effects on diabetes metabolic control in humans, and the analyzed trials in a systematic review had methodological limitations that preclude the use of therapy in clinical practice, such as small sample size, observational study design, and short-term treatment.^
19
^ Recently, a cross-sectional study found that habitual hot-tub bathing was associated with slight improvements in HbA1c and body mass index.^
44
^In contrast, a randomized crossover trial showed that 90 min of hot water immersion did not improve insulin sensitivity, markers of micro- and macrovascular functions, or circulating and intracellular HSP70 concentrations.^
45
^ There is a lack of consistent data in the literature, and, furthermore, the possible mechanisms by which benefits can be obtained remain unknown.

Since the HSR response is decreased in individuals with diabetes,^
13
^ we believe that improving the HSR may be important in preventing chronic complications associated with T2DM. This randomized clinical trial will determine the efficacy of HT compared to RT in improving HR when combined with conventional therapy in individuals with T2DM. Multiple HT and RT effects may contribute to a lower mortality risk in these individuals. Our study is the first to evaluate the efficacy of HT and RT in glucose, lipid, and inflammatory profiles, microbiota, and HR measurements in individuals with T2DM. Moreover, we will maintain the experimental protocol for 12 weeks, which is the time necessary to obtain changes in the main parameter of diabetes control, HbA1c.

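### The open-ended exclusion tests fitness for exercise only, although anyone eligible may be allocated to whole-body heat

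*Protocol article*

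**What the plan says.** The Eligibility criteria section gives a single list with no arm-specific part. After the named exclusions it closes off the remaining medical reasons with a general clause, "any condition that would prevent them from engaging in an exercise study". The named criteria include people who "report a history of myocardial infarction, cardiac illness, vascular disease, stroke", as well as pregnancy and breastfeeding, and participants must be "with controlled blood pressure, and no use of insulin".

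The Interventions section then states: "The participants will be randomized into the following intervention groups: control, RT or HT". For the heat arm it says: "Participants will be housed in an environmental chamber initially set at 55.0°C on three non-consecutive days of the week". Each session lasts 60 minutes. Pilot data showed a rise in core temperature of about 1.2°C and a fall in blood pressure, mainly diastolic. The section on body temperature assessment adds a rectal probe that participants insert themselves.

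On tolerability, the Safety and adverse events section says: "Heat therapy has been shown to be safe for most people".

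**The concern.** A catch-all exclusion exists to stop anyone being randomised who could not safely or practically receive one of the treatments on offer. In a trial with two active arms it has to cover both. Here it refers to one, and the trial is described as an exercise study although a third of participants are to receive passive heat.

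Two things are at stake. The first is safety: followed literally, the rule gives the screening clinician no ground to exclude a candidate who can exercise but should not be heated, unless the reason is one of the named criteria. The second is comparability of the arms. Unsuitability for heat has no consequence for someone allocated to control or resistance training (RT). In the HT arm it leads to stopped sessions, poor adherence or withdrawal. Intention-to-treat is the primary analysis, so these cases would enter it as untreated participants or as missing data in one arm only, in a trial planned with 22 per group.

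**Working it through.** No figure in the plan depends on this point. The check is a comparison of sections, followed by a note on scale.

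**1. Who can be allocated to heat?** Everyone eligible. The Interventions section randomises to control, RT or HT from one list, and no further screen for the HT arm is described.

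**2. Does fitness for exercise imply fitness for heat?** The protocol does not treat it so. The Introduction presents HT as an alternative for people who have difficulty exercising, so the two capacities are taken to be separable. The exposures also differ: loaded upper- and lower-body exercises on one side, and on the other an hour at high ambient temperature with a rise in core temperature, a fall in diastolic pressure and a rectal probe.

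**3. Which criteria already cover heat?**

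| Criterion | Bears on heat risk? |
|---|---|
| Myocardial infarction, cardiac illness, vascular disease, stroke | Yes, in part |
| Pregnancy, breastfeeding | Yes, in part |
| Controlled blood pressure | Yes, in part |
| Open-ended clause | Exercise only |

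What remains is any heat-specific reason outside the first three rows. The fourth row is where such a reason would normally be caught, and its wording does not reach it.

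**4. When do the heat-specific checks act?** Under Allocation, the envelope is opened at the start of treatment. Monitoring of rectal temperature, heart rate and blood pressure, the rule for stopping a session, and the urine and hydration check all belong to the heat sessions. All of them therefore follow allocation and apply in one arm only.

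**5. Scale.** Inputs from Statistical considerations: 22 per group and 10% dropout.
- One participant as a share of an arm: 1/22 = 4.5%.
- Planned dropout per arm: 0.10 × 22 = 2.2 participants.

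One such withdrawal would use 1/2.2 = 45% of the HT arm's dropout allowance, and two would use 2/2.2 = 91%. This shows how sensitive an arm of this size is. It does not predict how many cases will occur, because the document gives no rate.

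**The case against.** **A condensed article may leave detailed contraindications to the full protocol.** This is the strongest objection, and it disposes of any complaint that a list of heat contraindications is absent. It does not dispose of this point, which concerns the scope of a clause that is printed.

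**Much of the risk is already covered.** The named criteria apply in every arm, and a supervised maximal treadmill test is part of the evaluation. This stands as a limit on size. The treadmill test, however, examines exertion and not heat tolerance.

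**Unwillingness should surface before randomisation.** Participants are told about procedures and risks and sign consent before enrolment. This stands. Reluctance about the chamber or the probe is not the main route to trouble; medical unsuitability is.

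**The safety wording may be over-read.** A reader might infer from "Heat therapy has been shown to be safe for most people" that the protocol concedes a group for whom heat is unsafe. The text does not go that far: the exception it goes on to name is thermal discomfort, among mild and moderate events. The point here rests on the scope of the exclusion and not on that sentence.

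**Prior heat exposure.** Prior exercise is restricted, excluding people "if they had already been engaged in two or more planned and structured exercise sessions per week (in the last six months". A reader might infer that habitual sauna or hot-tub users should likewise be excluded because their heat shock response is already adapted. The documents do not support this. The Discussion reports that "habitual hot-tub bathing was associated with slight improvements in HbA1c and body mass index", which concerns neither the heat shock response nor the primary outcome. It then cites a randomised crossover trial of hot water immersion that found no improvement in HSP70. Randomisation also balances prior heat use in expectation. Such an exclusion would be a preference of the reviewer, not a correction.

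**Conclusion.** The point holds in a limited form. The eligibility rule as printed screens for one of the two interventions to which a participant may be allocated. Someone fit for exercise, free of the named conditions and unfit for heat for another reason is eligible, and this would come to light only after allocation and only in the HT arm.

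The consequences are a safety concern and withdrawal or non-adherence specific to one arm. Their size cannot be estimated from the document: no prevalence of heat-specific unsuitability is given, and the named criteria and the consent process both reduce it. The RT arm may have withdrawals of its own, so the net imbalance between arms is also unknown. A reader should not infer that heat-unfit people in general are admitted, or that a material bias in the primary outcome has been shown.

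The conclusion assumes that the printed list is the operative one. If the full protocol already words the clause for both interventions, only the article needs aligning. The change is worth making because it is cheap and acts before allocation.

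**What to change.** Reconcile the Eligibility criteria with the Interventions, Body temperature assessment and Safety sections, so that the open-ended exclusion refers to the ability to take part in either study intervention. State that it is judged for every candidate, whichever arm they later enter, before the allocation envelope is opened. The study physicians decide which conditions count; no list is proposed here.

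The cost is a short amendment and a few added questions at screening, with a few candidates lost there. If recruitment has begun, record the date from which the revised clause applies.
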